### Additional data collection concerning medication between measuring points

Data will be collected regarding changes in medication that occur between measuring points. The use of antidepressants will be monitored. There will be three categories: (1) no antidepressants; (2) use of a single antidepressant drug; (3) combinations of antidepressant drugs. Amounts of stops and starts will be registered as well as the total time for each category. Type of antidepressants according to official classification will be registered. The use of insulin will be categorized as: (1) no insulin; (2) single or multiple daily injections; (3) continuous subcutaneous insulin infusion. The duration of the period of each category will be monitored. All non-insulin antidiabetic drugs will be registered according to their official classification and the time that participants have used each drug will be monitored.

### Intention to treat analysis

#### Studies I and II

Differences at T0 between participants and nonparticipants fulfilling criteria will be analyzed regarding age, sex, self-reported depression and anxiety, alexithymia, self-image, clinical psychiatric diagnoses, smoking, physical inactivity, metabolic variables, medication and sick-leave status and will be thoroughly described. Levels of HbA1c will be determined for all patients who participate in the interventions, but decline to complete the questionnaires at T2, T3 (Study II only) or T4. At T4, all patients who participated at T0 will be asked for oral and written consent to participate in all the assessments, measurements and data collection that are included at T4. If full assessments are not possible we will collect data regarding HbA1c concentrations, mortality, diabetes complications and use of antidepressants.

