### Self-report instruments

#### Studies I and II

The Hospital Anxiety and Depression Scale will be used at all measuring points to assess self-reported anxiety and depression [4, 5, 32, 37–39]. The cut-off level for each subscale recommended by the constructors of this scale (≥8 points) will be used for inclusion in the intervention [38]. In a study that compared the Swedish version of the Hospital Anxiety and Depression Scale with a structured clinical interview for DSM-III criteria, the optimal cut-off level for screening was ≥5 points for both subscales [39].

The 20-item Toronto Alexithymia Scale will be used at all measuring points to assess alexithymia [4, 19, 32, 37, 40–42]. This scale consists of 20 statements rated from 1 to 5, and is based on three subscales: ‘difficulty identifying feelings’ (seven statements), ‘difficulty describing feelings’ (five statements) and ‘externally oriented feelings’ (eight statements).The recommended cut-off level (≥61 points) will be used for inclusion in the intervention [41, 42].

The affinity dimension of the Structural Analysis of Social Behavior assessment tool will be used to assess self-image [23, 35, 43]. This test consists of 36 statements with response options on a scale between 0 and 100; the results are summarized into eight clusters. High scores for the clusters ‘blaming self’, ‘hating self’ and ‘ignoring self’; and low scores for the clusters ‘accepting self’, ‘loving self’ and ‘nourishing self’ form a negative self-image. A negative self-image is defined as results below 284 points. The Structural Analysis of Social Behavior test will be used at T0 and at T4.

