### Primary and secondary outcome measures

In both studies, the primary outcome measure is the change in depression symptoms. Secondary outcome measures are changes in alexithymia and anxiety symptoms and self-image measures; changes in HbA1c concentration and midnight salivary cortisol concentration; use of antidepressants, and incidence of diabetes complications and mortality.

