#### Study II

The Kruskal–Wallis test will be used for changes in non-normally distributed variables (psychological symptoms and midnight salivary cortisol concentration).

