#### Studies I and II

A paired-samples *t* test will be used for continuous and normally distributed variables (HbA1c concentration). The associations between outcome variables and baseline characteristics will be modelled using linear regression analysis (HbA1c concentration, midnight salivary cortisol concentration, psychological symptoms); logistic regression analysis will be used for categorical outcomes (incidence of diabetes complications and use of antidepressants).

Cox proportional-hazards regression will be used to analyze effects on mortality. Missing values of the self-report instruments will be imputed using multinomial logistic regression on the other variables in the same subgroup [53]. Imputation will be performed for the depression and anxiety subscales of the Hospital Anxiety and Depression Scale if there are at most two missing items for each subscale; for the 20-item Toronto Alexithymia Scale if there is at most one missing item for each subscale (‘difficulty identifying feelings’, ‘difficulty describing feelings’ and ‘externally oriented feelings’) and for the Structural Analysis of Social Behavior tool if there is at most one missing item for each of the eight clusters. Statistical significance will be considered for *P* < 0.05.

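### The intention-to-treat section secures only secondary outcomes from patients who do not complete assessments, so the primary HADS depression comparison is complete-case as written and can be biased by non-response.

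*Protocol article*

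**What the plan says.** Under *Primary and secondary outcome measures*, "the primary outcome measure is the change in depression symptoms". Under *Self-report instruments*, "The Hospital Anxiety and Depression Scale will be used at all measuring points". Study II therefore has scores scheduled at T0, T1, T2, T3 and T4 in its randomised arms, and Study I at T0, T1, T2 and T4.

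The section *Intention to treat analysis* fixes two fallback collections:

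- For questionnaire refusers: "Levels of HbA1c will be determined for all patients who participate in the interventions, but decline to complete the questionnaires at T2", and likewise at T3 (Study II) and T4.
- At T4, after everyone seen at T0 has been invited to the full assessment: "If full assessments are not possible we will collect data regarding HbA1c concentrations, mortality, diabetes complications and use of antidepressants".

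Under *Statistical analysis* for Study II, the Kruskal–Wallis "test will be used for changes in non-normally distributed variables", which include the psychological symptoms. Study I adds the Wilcoxon signed rank test. On missing data the plan states "Missing values of the self-report instruments will be imputed using multinomial logistic regression on the other variables in the same subgroup", limited for HADS to cases "if there are at most two missing items for each subscale".

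Under *Power calculations for sample size*, about 10% questionnaire non-response is expected, and the response is to enrol 10% more patients. Under *Randomization and allocation* and *Schedule for assessments*, patients who refuse after allocation form a separate group (group 3 in Study I, group 4 in Study II) assessed at T0 and T4 only.

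**The concern.** The heading promises an intention-to-treat analysis, but the rules under it protect only secondary outcomes. A patient who returns no questionnaire has no HADS-D change. No stated rule supplies one, so the patient leaves the primary test. Enrolling more patients restores precision but does nothing about who is missing.

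The trial is open-label with a self-reported outcome, and the interventions differ in how acceptable they may be: the Discussion expects talking about emotions in a group to be stressful and BBAT to be accepted more readily. Non-response could therefore differ between arms and be related to how patients fared. The T2/T3 fallback is also worded for those who take part in the interventions, so it does not clearly cover the treatment-as-usual arm of Study II.

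At stake is a biased estimate of the primary effect, with either an inflated false-positive rate or lost power.

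**Working it through.** **1. The plan's own figures.** Inputs from the power section: difference 1.4, SD of change 2.8, alpha 0.05 (taken as two-sided), power 80%.

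- Study I, two-sample comparison: the normal formula gives 63 per arm and the noncentral t gives 63.8, so 64, as stated.
- Power at 21 per arm: 36.7% (normal) or 35.3% (t), against the stated 37%.
- Study II, one-way ANOVA with means 0, 0, 1.4: 59 per arm against the stated 60. Then 60 × 1.15 = 69 against the stated 70.

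The design figures reproduce, so the point does not rest on an error in them.

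**2. What happens to a patient with no later HADS questionnaire.**

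| Rule | Does it supply a HADS-D change? |
|---|---|
| Fallback at T2, T3, T4 for questionnaire refusers | No: HbA1c only |
| Fallback at T4 | No: HbA1c, deaths, complications, antidepressants |
| Imputation | No: at most two missing items per subscale |
| Rank tests on changes | No: both scores are needed |
| Enrolling 10% more | No: changes the number, not the selection |

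**3. Size of the possible bias.** Let d be the non-response rate in an arm, and g the amount by which non-responders' change is worse than responders' change. The true arm mean is the responder mean plus d × g, so the complete-case difference between arms A and B is off by

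bias = dA × gA − dB × gB, in favour of A when positive.

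The article gives d of about 10% overall, not by arm, and gives no g. I assume g between 1.4 and 2.8 points (0.5 to 1 SD of change).

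- 10% in both arms, same g: 0.10 × g − 0.10 × g = 0.
- 10% in both arms, g in one arm only: 0.10 × 1.4 = 0.14; 0.10 × 2.8 = 0.28.
- Rates 10 percentage points apart, same g: again 0.14 to 0.28.
- Illustration beyond the documented rate, 20% against 5%, same g: 0.15 × 1.4 = 0.21; 0.15 × 2.8 = 0.42.

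As shares of the target, 0.14/1.4 = 10%, 0.28/1.4 = 20% and 0.42/1.4 = 30%.

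**4. Effect on the test.** With 64 responders per arm the standard error is 2.8 × √(2/64) = 0.495. Using the noncentral t as an approximation to a two-arm rank comparison:

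| Bias (points) | Type I error | Power if the bias acts toward the null |
|---|---|---|
| 0 | 5.0% | 80% |
| 0.14 | 5.9% | 71% |
| 0.28 | 8.7% | 61% |
| 0.42 | 13.4% | 50% |

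**5. Cross-check by simulation.** Assumptions: no true effect, 77 per arm, HADS-D SD 3.5, correlations T0–T2 0.68, T2–T3 0.75 and T0–T3 0.60. These give a T0–T2 change SD of 3.5 × √(2 × 0.32) = 2.8, as stated in the article. With T3 loss driven by poor T0–T2 change in the therapy arm only, the complete-case bias was about 0.2 points at 10% loss (rejection 6–7%) and 0.3 to 0.44 at 20%. With the same outcome-related loss in both arms it was about zero.

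**6. What a likelihood-type analysis can recover.** When T3 loss depends on an observed T2 score, an estimate using T2 came within 0.03 of zero, but only because the loss was generated from data the model was given. When loss at T2 depends on the T2 change itself, only T0 and T1 precede it, both before intervention. Using them reduced the bias only from 0.20 to 0.13 points (10% loss) and from 0.43 to 0.30 (20% loss).

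**The case against.** The strongest reply is that analysis sets and wholly missing questionnaires belong in a statistical analysis plan, which is not shown, and that a journal article need not give them. This stands in part: such a plan could specify another model, and nothing in the article forbids one. But the article chose to state its intention-to-treat measures, tests and imputation limits, and these do not deliver what the heading says. What is collected from non-responders is protocol content, and no later plan can recover HADS-D scores that were never sought.

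A second reply is that the fallback is sound in itself: HbA1c and register data can be had without a questionnaire, while HADS-D needs the patient. That also stands. Collecting those data is good practice. The gap is that the primary outcome is not also sought in a shorter form and no rule covers its absence.

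A reader might go further and infer that non-response will bias the result in favour of the therapies, on the view that disappointed therapy patients stop answering and usual-care patients do not. The documents do not support this. They give no non-response by arm or by outcome, usual-care patients may also stop answering, and Study I has no usual-care arm. With equal, equally outcome-related loss the bias is zero.

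**Conclusion.** The point holds in this form: under the stated rules the primary HADS-D comparison is complete-case despite its heading, and it can be biased if non-response is related to outcome differently across arms. At the documented 10% non-response the assumed scenarios give 0 to about 0.3 points, at most about 20% of the 1.4-point target. This rests on an assumed responder/non-responder gap of 1.4 to 2.8 points and on the t approximation to the rank test. The direction is unknown.

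Losses above 10% are illustrations only. A reader might also infer that a mixed model removes the problem; it does so only so far as earlier scores explain the loss, which is less likely at T2.

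Moving post-allocation refusers out of their randomised arm, with no T1 to T3 assessment, is a further departure from intention to treat, on top of questionnaire non-response. The whole is worth correcting because Study II had not begun recruiting and the change is cheap.

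**What to change.** 1. **Collection.** In *Intention to treat analysis*, add that the HADS depression subscale alone is offered when the full battery is declined, alongside the existing fallback data. Apply this in all randomised arms, including treatment as usual: at T2, T3 and T4 in Study II, and at T4 only in Study I, whose T2 is past.
2. **Analysis.** In *Statistical analysis*, analyse HADS-D in all randomised patients in their allocated arm, using every available HADS visit. Use a mixed model for repeated measures, or multiple imputation with earlier HADS-D, HbA1c and antidepressant use as auxiliary variables. Keep the rank test on completers as a sensitivity analysis.
3. **Refusers.** Keep patients who refuse after allocation in their randomised arm for this analysis. Under the present schedule they contribute T0 and T4 scores, so any T2 or T3 comparison leans on the model for them.

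Cost: changes of wording, one short extra contact per non-responder and somewhat more analysis work. The analysis assumes data missing at random, which is more credible for loss at T3 and T4 than at T2, where only pre-intervention scores are available. Step 1 therefore matters most at T2.

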### Written and oral informed consent

Written and oral informed consent will be received from each participant in both studies at T0 and at T4, and oral consent after allocation to intervention (Figs. 2 and 3).

The studies were approved by the Regional Ethical Review Board of Linköping University, Linköping (registration no. M120-07, T83-08).

### Self-report instruments

#### Studies I and II

The Hospital Anxiety and Depression Scale will be used at all measuring points to assess self-reported anxiety and depression [4, 5, 32, 37–39]. The cut-off level for each subscale recommended by the constructors of this scale (≥8 points) will be used for inclusion in the intervention [38]. In a study that compared the Swedish version of the Hospital Anxiety and Depression Scale with a structured clinical interview for DSM-III criteria, the optimal cut-off level for screening was ≥5 points for both subscales [39].

The 20-item Toronto Alexithymia Scale will be used at all measuring points to assess alexithymia [4, 19, 32, 37, 40–42]. This scale consists of 20 statements rated from 1 to 5, and is based on three subscales: ‘difficulty identifying feelings’ (seven statements), ‘difficulty describing feelings’ (five statements) and ‘externally oriented feelings’ (eight statements).The recommended cut-off level (≥61 points) will be used for inclusion in the intervention [41, 42].

The affinity dimension of the Structural Analysis of Social Behavior assessment tool will be used to assess self-image [23, 35, 43]. This test consists of 36 statements with response options on a scale between 0 and 100; the results are summarized into eight clusters. High scores for the clusters ‘blaming self’, ‘hating self’ and ‘ignoring self’; and low scores for the clusters ‘accepting self’, ‘loving self’ and ‘nourishing self’ form a negative self-image. A negative self-image is defined as results below 284 points. The Structural Analysis of Social Behavior test will be used at T0 and at T4.

### Measurements

#### Study I and II

According to the Swedish national guidelines for diabetes management in 2009, the recommended goal for treatment was for HbA1c concentrations of less than 52 mmol/mol. However, since goals should be individualized, a higher cut-off value was chosen in this study: venous HbA1c concentration (IFCC units) ≥62.5 mmol/mol, (Mono-S ≥7 %, NGSP ≥7.87 %) [44]. Analyses will be performed with high pressure liquid chromatography, (HPLC - variant II, Turbo analyzer, Bio-Rad®, Hercules, CA, USA) [45].

Serum lipids will be analyzed using the enzymatic colour test (Olympus AU®, Tokyo, Japan). Blood lipids and HbA1c will be analyzed at the Department of Clinical Chemistry, Växjö Central Hospital.

Blood pressure, waist circumference, weight and length will be measured by a nurse, according to standard procedures. Abdominal obesity is defined for men as waist circumference ≥1.02 m. and for women as waist circumference ≥0.88 m [4, 5]. General obesity is defined as body mass index ≥30 kg/m^2^ for both sexes [4].

Midnight salivary samples will be collected between 23.30 and 00.30 hours using a Salivette sampling device [5, 46–49] (Salivette®, Sarstedt, Nümbrecht, Germany). Assays will be performed at the Department of Clinical Chemistry, Lund University Hospital, Lund, using Roche Cobas Cortisolassay®, a competitive electrochemiluminescence immunoassay [5, 46–49], using an Elecsys 2010 immunoanalyzer system (Roche Diagnostics, Mannheim, Germany). Patients will receive written and oral instructions before sampling [5].

### Data collection

For both studies, data regarding patients’ diagnoses, diabetes complications, life style factors, medication, psychotherapy, diabetes-related medication and antidepressants and sick leave will be collected from the Swedish national diabetes register, from medical records from the departments of internal medicine, ophthalmology and psychiatry, and from primary care centres. Data from all hospital clinics, the psychiatry department and all primary care centres (including psychotherapy obtained in primary care) are available as they are connected to the same computer system (Cambio Cosmic ®). Mortality data will be collected from the Swedish causes of death register.

### Definitions of diabetes complications and severe hypoglycemia episodes

Foot complications are defined as neuropathy, angiopathy, previous or current diabetes foot ulcer, foot infection, foot deformity, arthropathy, or amputation of the lower limb [4]. Diabetes retinopathy is defined as nonproliferative or proliferative retinopathy with microangiopathy changes, as viewed by fundus photography through a dilated pupil [4]. Macrovascular complications are defined as ischemic heart disease (angina pectoris, previous myocardial infarction, percutaneous transluminal coronary angioplasty or coronary artery bypass graft surgery); stroke or transient ischemic attack [4]. End-stage renal disease is defined as a state where dialysis or a renal transplant is necessary [50]. A severe hypoglycemic episode is defined as one in which help is needed from another person owing to hypoglycemia; episodes occurring during the previous 6 months will be registered [4, 5].

### Definitions of smoking and physical inactivity

Patients are defined as smokers if they have smoked any amount of tobacco during the last year [4, 5]. In the Swedish national diabetes register, physical activity is categorized into four groups: moderate activities for ≥30 minutes, less than once a week, once a twice a week, 3–5 times/week, or daily. Patients are defined as physically inactive if they perform moderate activities, such as 30 minutes of walking, less than once a week [4, 5].

### Affect school and script analysis – a psycho-educational method

#### Studies I and II

The intervention comprises eight weekly sessions of a group with five to seven participants (‘affect school’) with two instructors followed by ten weekly individual sessions (‘script analysis’). Two psychotherapists and one physician are recruited as instructors for both studies. They were trained together to become instructors by the constructors of the ASSA method, and have been instructors together in several ASSA groups. The same two instructors participate in all eight group sessions, which render three possible combinations: physician and psychotherapist I; physician and psychotherapist II; and psychotherapist I and psychotherapist II. The patients could be considered clustered within the pair of instructors. Patients will also be clustered by the set of five to seven participants included in each group. As depression is the main outcome measure we will test associations between depression symptoms, instructors and groups. Only one room will be used for all group sessions in each study.

At each affect school session a specific information handout is distributed, containing affect and script theory and the topics for the affect discussion. The scheme for the affect school sessions is presented in Table 1. During the first part of each affect school session the participants are instructed on general affect theory, and specific theory regarding the particular innate affects that are the topics for the session, followed by script theory. During the second part, the affect discussion, participants are encouraged to tell single-event autobiographical memory narratives; this exercise is considered important in psychotherapy [51]. The goal of the affect school is to achieve increased emotional awareness and verbal expressiveness. The affect theory presented during the affect school group sessions is essential for the script analysis, and we consider that participation in at least five group sessions is necessary to obtain an understanding of the theory. Persons with lower participation rate will not be offered script analysis. The total participation rate in ASSA will be counted.

**Table 1 Tab1:** General programme for the eight affect school sessions

*Affect theory*	
General affect theory is presented at all sessions. Specific affect theory for innate affects is presented according to the following program for the eight sessions.	
1) Joy	
2) Fear	
3) Interest and surprise	
4) Shame	
5) Anger	
6) Distaste and dissmell	
7) Distress	
8) Pain	
*Script theory presented at each session*	
1) Affects and experiences together form the individual scripts.	
2) How we act in different situations and how we interpret experiences depending on our scripts.	
3) Scripts are formed by family rules and common cultural rules for how affects should be handled.	
4) Intensity and expressions of emotion are controlled by scripts.	
5) Affects can be completely suppressed and thereby unconscious.	
Break for coffee or tea	
*Affect discussion*	
Main topics for the affect discussions follow the programme for the eight sessions. Questions used in the affect discussions are:	
1) Tell of a situation when you felt…	
2) How do you know that you feel…?	
3) Do you feel it in a particular place in the body?	
4) Does it happen often?	
5) How do you know that someone else is…?	
6) Can you understand and accept another person’s…?	
7) How does… influence your personal relationships?	

During the individual sessions (script analysis), the patient is encouraged to focus on one or two affects that he or she finds particularly difficult to handle, and the patient’s scripts for handling these affects are discussed. These sessions are performed by psychotherapists or social counsellors.

Here follows a short description of the affect theory that will be presented during the group sessions. A more complete description is presented elsewhere [37]. Essential in the affect school are the five concepts of affects, feelings, emotions, mood and scripts. Affects are the innate, unconscious and strictly biological portions of emotions. Each affect has a specific programme involving face mimicry, body gestures, voice and autonomous nervous and hormone system physiology. The innate affects are enjoyment-joy, interest-excitement, surprise-startle, fear-terror, anger-rage, distress-anguish, shame-humiliation, distaste and dissmell. Pain has features of both an affect and a drive. Affects are important messengers to the self. The primary functions of the innate affects are to regulate drives, such as hunger and sexuality. The secondary functions are to regulate other affects. *Feelings* are the conscious portions of emotions. *Emotions* reflect biography. A triggered affect evokes memories of earlier situations and relationships where this affect has been triggered before and, in addition, other affects triggered in the earlier situations will be triggered again in the present situation. An emotion lasts as long as memory continues to trigger the involved affects. *Mood* is defined as a persistent state of emotion. Anxiety and depression are subsequently mood disorders. *Scripts* are learned patterns to handle emotions.

